### Interventions

#### Control group

Participants randomized to this study arm receive no intervention. They continue to receive monthly social assistance payments according to the British Columbia Ministry of Social Development and Social Innovation disbursement schedule.

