#### Staggered social assistance disbursement (staggered

Participants in the ‘staggered’ intervention study arm have access to their social assistance payments on a monthly basis on a day that does not fall during government cheque issue week and that is not the same as all other participants in the staggered arm. Due to the variation in government cheque issue day timing, which ranges from the 16^th^ to the 29^th^ of the month, individual cheque issue is allocated relative to government cheque issue day (e.g., Tuesday the week after cheque issue). Participants undergo a transition period during which they receive their social assistance up to 7 days later each month until they reach their study cheque issue date. This transition period ensures that participants do not have a time period between payments any longer than the longest period between payments on the government schedule, which is 35 days. To facilitate timely transitions to the new disbursement schedule within the timeframe of the intervention, possibilities for individual cheque issue is are limited to business days during the first and second week following government cheque issue day. This allows for 10 possible payment schedules for participants in the staggered arm. The exact date of disbursement is determined at random through a second randomization procedure. Study staff provide each participant with a detailed payment schedule to assist participant recall.

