#### Staggered and split and social assistance disbursement (staggered and split)

Participants in the ‘staggered and split’ intervention study arm have their social assistance payments released twice a month on days that do not fall during the week of government cheque issue. The days of income assistance receipt are spaced 2 weeks apart and determined at random. As with the staggered intervention arm, individual cheque issue days are established in relation to government cheque issue day and participants transition to their new schedule incrementally. The first individual cheque issue day falls in the week following government cheque issue, with the second occurring on the corresponding day of the week 2 weeks later. This could be, for example, Tuesday of the week following government cheque issue day and Tuesday 2 weeks after that day. This allows for five randomization possibilities for the staggered and split intervention study arm. Participants are again provided with a schedule of their individual cheque issue days for the duration of their study participation.

The change in social assistance payment schedules for both intervention arms is managed through Pigeon Park Savings, which has developed a system, in conjunction with standard social assistance direct deposit services from the British Columbia Ministry of Social Development and Social Innovation, that varies when individuals have access to their social assistance payments. Social assistance payments are directly deposited into the participant’s account, and the system “locks” their payment so that these funds cannot be withdrawn. Money is “unlocked” according to the participant’s disbursement schedule that determines both the timing and frequency at which payments are released. Intervention arm participants can develop personalized arrangements that ensure access to essential funds at specific times to prevent housing instability or payment default. A study liaison at Pigeon Park Savings manages account creation, direct deposit requests to the Ministry and the implementation of holds and releases of funds. Accounts include unlimited withdrawals and a bank card with no-fee withdrawals at credit union automated teller machines. Pigeon Park Savings banking fees are charged at a rate of $5/month, and individuals are not required to pay this fee while they are enrolled in the study.

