#### Drug use (timeline follow back; primary outcome measure)

The TASA study’s primary outcome is increased intensity of drug use on government cheque issue day (i.e. a binary outcome). Participant drug use is considered to have intensified if, in the 3 days starting with government cheque issue day, a participant increases by 40 %: (1) the daily frequency of non-cannabis drug use; (2) the street value of drugs consumed; or (3) the number of non-cannabis substances used, including alcohol and illicit prescription opioids, all compared to the average frequency, value of drugs used or number of substances used on all other days of the calendar month. For example, if an individual uses crack cocaine once daily on non-cheque issue days and does not use methamphetamine, but increases uses crack cocaine 3 times per day and methamphetamine once per day on the 3 days beginning with cheque issue day, they will have intensified their use according to the first and second criteria. These cut points were selected based on prior empirical studies [8] and our intention to capture changes among high-intensity users that could be overlooked if more blunt measures common to RCTs among PWUD, such as daily drug use [44], are used. Staff gather data measuring the primary outcome using the Timeline Follow Back (TLFB) instrument, a reliable, validated, calendric instrument that collects daily information on drug use patterns, including drugs used and frequency of use [30, 31]. We additionally collect participant estimates of the street value of drugs used as a proxy for quantity or dosage of drug consumed, which may not be captured by drug use frequency measures [45, 46]. We also use daily TLFB drug use data to assess our key secondary outcome of intensified drug use on individual cheque issue days, identified using the same frequency, street value or number of drugs criteria as intensified drug use on government cheque issue day.

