### Participant safety

The design of the current trial does not involve any change in the amount of social assistance provided to participants, and we therefore do not anticipate any negative changes to their financial well-being. However, desynchronizing social assistance may disrupt money management strategies, potentially interfering with the payment of expenses. Importantly, most participants in the TASA study have the rent portion of their social assistance paid directly to their landlords. Participants who have rent or other expenses can make arrangements on a case-by-case basis with Pigeon Park Savings to ensure the availability of funds at the appropriate time. Additionally, for staggered and split arm participants, receiving multiple payments per month may result in more frequent periods of intensified drug use, albeit these periods will likely be shorter or less intense given that less money will be disbursed at any one time. For intervention participants, there may also be challenges transitioning onto or off of a new social assistance payment schedule at the start or end of the study period. To mitigate this concern, study staff members can provide referrals to financial management support services as appropriate. We do not anticipate the study will expose participants to unusual risks. Nevertheless, we monitor participant safety as a part of each bi-weekly participant assessment, including considerations of food and housing insecurity, exposure to violence, access to critical health and social services and other emerging issues. We follow standard reporting procedures for adverse events and serious adverse events [64], including oversight from an external, independent Data Safety and Monitoring Committee (DSMC). Participants are able to withdraw from the intervention, the study, or both at any point, and may be withdrawn from either by investigators in the event of concerns over safety.

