### Data analysis

#### Quantitative analyses

At the conclusion of the trial, the primary and secondary endpoints will be assessed via intention-to-treat analyses [67], including all patients randomized regardless of compliance with the intervention protocol. Sub-analyses will include a modified intention-to-treat analysis that will use all participants with at least one follow-up [67, 68]. First, we will compile descriptive characteristics of the sample, assessing for systematic differences in key characteristics across study arms using the Chi-Square test for binary variables and the Mann-Whitney *U* test for continuous variables. The primary outcome of interest will be derived from TLFB information as a repeated binary variable (intensified drug use on the 3 days beginning with government cheque issue day vs. not) and will be quantified as the proportion of individuals TASA participants reporting increased drug use during this period at each government cheque issue. This outcome, and other secondary outcomes similarly quantified will be examined using pooled generalized linear mixed effects models, with binomial distribution and logit link specified to produce unadjusted and adjusted odds ratios and 95 % confidence intervals. Other secondary outcomes of interest, quantified as counts of the number of occurrences over the course of the observation period (e.g., hospital ED admissions), will be examined using generalized linear mixed-effects model, with a Poisson distribution and a log link specified for count data with corrections for overdispersion, including a Vuong test for overdispersion and, where indicated, the use of a negative binomial model [69]. All analyses will include binary indicators of study arm allocation to assess for systematic differences in primary and secondary outcomes of interest across study arms. Multivariate analyses will be adjusted for: (1) binary indicators of the type of income assistance the participant receives; (2) an indicator variable for whether the individual changed their financial service provider to Pigeon Park Savings (PPS) at the start of the study to control for the effect of becoming a PPS client; (3) socio-demographic characteristics, including gender, ethnicity and age; indicators of addiction treatment enrollment and DTES residency, and (4) a categorical variable for the number of days between government cheque issue and their study visit to account for differences in recall reliability. As is common in RCT analyses [70, 71], missing assessments of intensified drug use will be treated as positive and tested for sensitivity to this assumption [72, 73]. Additional sensitivity analyses will include: (1) a modified intention-to-treat analysis using all participants with at least one follow-up assessment [74]; and (2) per-protocol analyses of participants who maintain enrollment in the intervention [75, 76].

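### On individual cheque days, the split arm's reference days include its other payday, so split needs a true rise of about 47%, not 40%, to be flagged

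*Protocol article*

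**What the plan says.** The section on drug use (Timeline Follow Back) defines the primary outcome. Use is intensified if, "in the 3 days starting with government cheque issue day, a participant increases by 40" per cent in frequency, street value or number of substances, "all compared to the average frequency, value of drugs used or number of substances used on all other days of the calendar month". The same section then introduces the "key secondary outcome of intensified drug use on individual cheque issue days, identified using the same frequency, street value or number of drugs criteria" as the government-day outcome.

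The number of paydays differs by arm. Of control participants the article says "They continue to receive monthly social assistance payments". Staggered participants "have access to their social assistance payments on a monthly basis". Staggered and split participants "have their social assistance payments released twice a month", two weeks apart. In both intervention arms the individual paydays fall outside government cheque week.

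Under Quantitative analyses the primary outcome is a repeated binary variable with one record per government cheque issue, and "other secondary outcomes similarly quantified will be examined using pooled generalized linear mixed effects models" with a logit link. The Objectives commit to comparing the interventions with each other and with control. Participant safety recognises that "receiving multiple payments per month may result in more frequent periods of intensified drug use", and the Background raises the same possibility.

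**The concern.** A rule built for one payday a month is applied to an arm that has two. In control, the reference days contain no other payday. In split they contain a second 3-day payday window. If use rises there too, the reference average goes up and the 40% bar is harder to reach. The same behaviour on a payday can then count as intensified in control and not in split.

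This is the outcome that shows whether a person's own payment cues heavier use, and the split arm raises that question most sharply. A measurement rule that lowers the split arm's rate by construction would look like a benefit of splitting. The article itself expects split-arm periods to be shorter or milder, so the artefact would add to any real effect in the expected direction and could not be told apart from it.

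**Working it through.** **Inputs from the article.** Window 3 days; threshold ratio 1.40; reference is all other days of the calendar month; paydays per month 1, 1 and 2 in control, staggered and split; split paydays 14 days apart, so the two windows do not overlap. The article gives no expected rate or power for this outcome. Its sample size (65 completers, 91 randomised per arm) concerns the government-day outcome and is not affected.

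**Assumptions.** A 30-day month containing both split windows; use of 1 on ordinary days and *m* on payday-window days, equal in all arms; control's individual payday is the government day.

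**Step 1: the bar with one payday.** The reference is 27 ordinary days with mean 1. A participant is flagged if *m* ≥ 1.40.

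**Step 2: the bar in split.** The reference is 24 ordinary days plus 3 days of the other window, with mean (24 + 3*m*)/27. The rule becomes 27*m*/(24 + 3*m*) ≥ 1.40, so 22.8*m* ≥ 33.6 and *m* ≥ 1.474. For months of 28 and 31 days the bar is 1.481 and 1.471. A true ratio of 1.40 is recorded as 1.34, and 2.0 as 1.80.

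**Step 3: if use also rises by *m* in the 3 days from government cheque day.** That window is control's own payday window, so control stays at 1.40. Staggered has one other raised window in its reference, as in step 2, and needs 1.474. Split has two: 27*m*/(21 + 6*m*) ≥ 1.40, so 18.6*m* ≥ 29.4 and *m* ≥ 1.581.

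**Step 4: size per payday.** Simulation of 200,000 person-months per setting, Poisson daily frequency, frequency criterion only, no government-day rise, equal payday behaviour in both arms:

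| Mean uses/day | True rise | One payday | Split, per payday | Gap (points) |
|---|---|---|---|---|
| 1 | none | 25.2% | 25.2% | 0.0 |
| 1 | 1.5x | 52.8% | 48.8% | 4.0 |
| 1 | 2x | 74.8% | 68.3% | 6.5 |
| 3 | none | 14.0% | 14.0% | 0.0 |
| 3 | 1.5x | 57.8% | 50.8% | 7.0 |
| 3 | 2x | 89.1% | 81.3% | 7.8 |
| 6 | none | 6.6% | 6.7% | -0.1 |
| 6 | 1.5x | 62.0% | 52.0% | 10.0 |
| 6 | 2x | 96.1% | 90.0% | 6.1 |

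A separate simulation that flags a window on any of the three criteria (3 uses a day, 1.5x) gives 78.2% against 72.0%, a gap of 6.2 points.

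**Step 5: varying the rise between people.** With a log-normal payday multiplier (SD 0.4 on the log scale, 3 uses a day) tuned so that control is near the article's assumed 85%, the result is 84.5% against 80.5%, an odds ratio of about 0.76. Near 65% it is 64.3% against 59.7%, an odds ratio of about 0.82. No true difference exists in either case.

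**Step 6: correcting the reference.** Leaving the other payday window out gives 84.5% against 84.4%, and 64.3% against 64.3%. Leaving out the government window as well (3 uses a day, 1.5x) gives 58.2% against 58.5%.

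**The case against.** The strongest reply is that carrying over the reference period is partly inference. The sentence on individual cheque days names the three measures and does not restate the reference days. The article's own worked example uses days without a cheque as the baseline, and the introduction to Measures separates such days from government and individual paydays. That stands as a reason to call this a wording to be fixed, not a settled error. But the only reference the article defines is all other days of the month, the new outcome is identified by the same criteria, and nothing removes a second payday. The literal reading is the likelier one.

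A second reply concerns size. The multiplier and use levels are assumed, and a 1.5x rise lies close to the 1.47 bar, where the artefact is prominent. In a check using all three criteria the gap was 2 to 4 points at 2x and at most 1 point at 3x. This too stands: the effect is moderate and depends on where true rises lie.

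Three stronger readings are tempting, and the article does not support them.

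- **The rule could equally make split look worse.** That needs a month to count as positive when either payday qualifies. The article states no such scoring. Its repeated binary outcome, one record per cheque issue, points to scoring by payday.
- **Two windows a month is itself a bias.** A mixed model handles unequal numbers of records, and the chance of intensified use per payment is a proper target. Overall monthly drug use is a separate pre-specified secondary outcome.
- **A count of intensified windows should therefore be the main outcome.** With no payday effect and 3 uses a day, the count was 0.15 a month with one payday and 0.30 in split. It would show a doubling when paydays change nothing.

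**Conclusion.** The concern holds for the reference days. As written, the rule sets a true bar of about 1.47 in split against 1.40 in an arm with one payday, and it favours split by roughly 4 to 10 points per payday for true rises of 1.5 to 2 times. There is no gap without a payday effect, and little for large rises when use is frequent. If government-day use rises too, staggered is affected as well, so control and staggered should not be treated as interchangeable on this outcome.

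The bar is plain arithmetic given equal payday rises and both windows in one calendar month. The percentage gaps rest on assumed Poisson use of 1 to 6 a day and, in the table, on the frequency criterion alone. The conclusion also rests on the literal reading of the reference period and on scoring by payday. It touches a key secondary outcome and the comparisons of split with the other two arms. The primary outcome's sample size is unaffected. The change should be made, given its low cost.

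**What to change.** State that, for intensified use on individual cheque days, the reference average in every arm comes from days outside all individual payday windows and outside the 3-day government cheque window. Keep the per-payday binary outcome and the logit mixed model as the main analysis, and say explicitly that each payday is one record.

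Because the article names more frequent intensified periods as a risk of splitting, also report the number of intensified payday windows per cycle by arm, descriptively. Note beside it that split has two windows, and so about twice as many chance flags even if paydays have no effect.

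The cost is a change of wording and derivation code on daily data already collected. In a 30-day month the reference falls from 27 days to 21 in split (27 - 3 - 3) and to 24 in staggered (27 - 3), and stays at 27 in control. The shorter reference makes the ratio slightly noisier, most noticeably when use is infrequent.

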#### Drug-related activities and exposures

A range of activities and exposures has been associated with increased risk of drug-related morbidity and mortality as well as social and community harms [47–51]. To support analyses of secondary outcomes of interest, past six month (baseline) and past 2 week (baseline and follow-up) self-reported measures for drug use-related activities and exposures include: changes in drug use patterns (e.g., binge or greater than average drug use); distributive and acquisitive syringe, crack pipe or drug equipment sharing; receiving an assisted injection; public injection and non-injection drug use; and non-fatal overdose. Questionnaire items have previously been verified for use in the current study context through longstanding cohort studies involving PWUD [52].

#### Addiction treatment enrolment and harm reduction service use

Past six month (baseline) and past 2 week (baseline and follow-up) data on addiction treatment enrolment are collected for secondary analyses about addiction treatment interruption. Questions include the type of addiction treatment, interruptions to ongoing opioid assisted or other treatments, missed visits, the reasons for addiction treatment interruption (if any), and the impacts of treatment interruptions or missed visits (e.g., relapse, withdrawal). We additionally ask participants about past six month (baseline) and past 2 weeks (baseline and follow-up) use of Insite, a local supervised injection facility (SIF), given the association between exposure to the SIF and significant improvements in in morbidity, mortality, uptake of addiction treatment uptake and measures of public order [53].

#### Police contact and illegal activity

While drug market enforcement has been shown to have adverse public health and social impacts [54], studies have also identified police as critical supports for public health and community safety initiatives [55]. We collect data on all police interactions, and the measures used in the current study facilitate distinctions between different types of police contact (e.g., service referral, arrest), as well as participant perceptions of the reason for contact. In support of economic analyses, we also collect data about engagement in illegal activity to assess any changes in the costs of criminality and victimization as a result of the intervention, with past six month (baseline) and past 2 week (baseline and follow-up) recall periods.

#### Exposure to violence

Consistent with previous analyses documenting the relationship between socio-economic marginalization and exposure to violence [56], the TASA study also seeks to document whether varying social assistance payments impacts participants’ exposure to violence. The study instrument includes measures to identify the frequency, timing and type of violence victims were exposed to, the type of perpetrator (e.g. stranger, intimate partner) and whether the participant sought police or medical attention. The study solicits analogous information regarding the perpetration of violence.

#### Health service utilization

Several key secondary outcomes of the TASA study are linked to whether the study intervention can reduce or smooth health service utilization. Previously identified health service impacts of synchronized social assistance include ED, EDMH or SUH admissions [7, 11–13, 19, 57]; discharges against medical advice directly prior to cheque issue [7, 9, 12]; health service access barriers linked to elevated demand [6]; and interruptions to ongoing medical care [9, 22]. In support of these assessments the study instrument collects past six months (baseline) and past 2 weeks (baseline and follow-up) information on which health services were accessed, whether participants attempted but were unable to access a service, the timing and reason for encountering service access barriers and whether participants missed medical appointments around cheque issue. We additionally collect information on whether, if hospitalized, participants left hospital against medical advice, as well as the reasons for and timing of their departure.

